#### Exclusion criteria

2.2.2

The contents of the case group and the control group are consistent, and the three parts of the experiment are identical, except that Item (h) is absent in the second part. (a) Patients with mental disorders or impaired consciousness; (b) Pregnant, lactating women and women preparing for pregnancy; (c) Heavy smokers, defined as those smoking at least 20 cigarettes (1 pack) per day; (d) Complicated with non-soft tissue chronic injury diseases such as lumbar intervertebral disc herniation, spinal stenosis and intraspinal lesions; (e) Pain caused by lumbar spine surgery, trauma, rheumatoid arthritis, etc.; (f) Malignant tumors, acute infectious diseases, severe skin diseases, rheumatism and immune diseases, complicated with severe heart, liver and kidney diseases; (g) Patients participating in other external therapies, medications and other treatments that may affect the judgment of results; (h) Contraindications to fNIRS monitoring such as a history of craniocerebral surgery, cranial defects and phobia of headgear wearing.

#### Criteria for elimination, termination and attrition

2.2.3

The contents of the case group and the healthy group are consistent, and the three parts of the experiment are identical. (a) Those who did not meet the inclusion/exclusion criteria or concealed their medical history after enrollment; (b) Those who failed to follow the prescribed intervention measures and showed poor compliance; (c) Those who developed serious adverse reactions during the intervention, or experienced exacerbation of underlying diseases and certain complications; (d) Those who withdrew voluntarily or lost contact.

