#### Randomization and blinding

2.3.2

Randomization is standardized in this study in combination with the design characteristics of the three parts of the experiment: The first part is a case–control observational study. After screening through strict inclusion and exclusion criteria, the case group (patients with lumbar muscle strain) and the control group (healthy people without lumbocrural pain) are selected from the eligible population by simple random sampling (15 cases in each group) to ensure sample representativeness, with no inter-group random allocation involved. The second part is a cross-over design study, in which 24 patients with lumbar muscle strain are divided into 3 groups (8 cases in each group) by complete randomization, receiving three sequences of rolling manipulation intervention with low-medium-high, medium-high-low and high-low-medium pressure, respectively. The third part is an interventional trial involving 69 participants in total. 46 patients with lumbar muscle strain are stratified by age and disease duration and then divided into a case intervention group (rolling manipulation intervention, *n* = 23) and a case control group (health education intervention, *n* = 23) by the random number table method; additionally, 23 healthy controls are selected by simple random sampling.

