This study adopts a partial blinding method to control bias, and supplements standardized training for operators to reduce operation bias: At the participant level, in the crossover design of the second part, participants are unaware of the pressure level and intervention sequence. In Part 3, participant blinding to the type of intervention is not feasible because the case intervention group receives manual rolling manipulation whereas the case control group receives health education. Participants are not informed of the study hypotheses or the expected superiority of either intervention. Outcome assessors and statistical analysts remain blinded to group allocation. Data collection is performed by full-time researchers who do not participate in the interventions, and statistical analysts receive coded anonymous data; neither is aware of the grouping information. All operators receive unified standardized training for 3 times (2 h each time), including the calibration of manipulation pressure, frequency and operation position, and only pass the assessment (the consistency of manipulation parameters ICC>0.8) can they perform the intervention independently. Blinding is maintained by separating the intervention and data collection settings and formulating confidentiality protocols. The blind is only broken in accordance with procedures and documented in detail upon approval by the ethics committee in special circumstances such as the occurrence of serious adverse reactions in participants.

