### Sample size calculation

2.8

Based on the core research objectives and design types of the three parts, this study is overall planned as follows:

The first part is an observational study, with the fNIRS-derived cortical hemodynamic response (HbO/HbR changes) as the primary outcome. Based on repeated measures analysis of variance (effect size *f* = 0.286, α = 0.05, 1−β = 0.8) (30), G*Power 3.1.9.7 calculation showed that 12 cases are needed in each group. Considering a 20% attrition rate, 15 cases are included in both the healthy control group without lumbocrural pain and the lumbar muscle strain case group, with a total of 30 cases.

The second part is a cross-over design. The sample size was estimated based on the median frequency (MF) of the surface electromyographic (sEMG) signals, one of the primary electromyographic outcomes for screening the optimal pressure. Referring to our previous study on rolling manipulation in patients with lumbar muscle strain (13), the within-individual standard deviation of sEMG frequency was 17.09 Hz and the intraclass correlation coefficient was 0.5. Repeated Measures ANOVA combined with Greenhouse–Geisser corrected F test (α = 0.05, 1-β = 0.8) was adopted. PASS 2021 software calculation showed that 17 cases are needed. Considering a 20% attrition rate, 24 patients with lumbar muscle strain are included and randomly divided into 3 group sequences.

The third part took the change in the Oswestry Disability Index (ODI) from baseline to immediately after the 6th intervention as the primary clinical endpoint for the comparison between the case intervention group and the case control group. Based on a two-independent-sample design, in which the expected between-group difference (μ2 − μ1 = 10) and the standard deviation (σ = 9) were derived from a previous study on massage combined with functional exercise for chronic lumbar muscle strain (31), With α = 0.05 and 1 − β = 0.80, the calculation showed that 18 patients were required in each group. Considering a 20% attrition rate, 23 patients with LMS will be enrolled in the case intervention group and 23 in the case control group, resulting in a total of 46 patients with LMS. In addition, 23 healthy controls will be enrolled as a reference group for the fNIRS and biomechanical comparisons. Therefore, Part 3 will include 69 participants in total, comprising 46 patients with LMS and 23 healthy controls.

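### The Part 3 elimination criteria do not separate stopping the intervention from leaving the analysis, so the primary ODI comparison could be made on a group selected after randomisation

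*Protocol article*

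**What the plan says.** All references are to the protocol article.

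- **Section 2.2.3** is headed "Criteria for elimination, termination and attrition". It gives a single list of four entries, the same for patients and healthy participants and for all three parts. Entry (a) is ineligibility or concealed history that comes to light after enrolment. Entry (b) is "Those who failed to follow the prescribed intervention measures and showed poor compliance". Entry (c) is "Those who developed serious adverse reactions during the intervention, or experienced exacerbation of underlying diseases and certain complications". Entry (d) is "Those who withdrew voluntarily or lost contact". No entry is tied to a particular one of the three actions in the heading.
- **Section 2.3.2** allocates the 46 Part 3 patients, after stratification, "by the random number table method", with 23 in each arm. It also states that "participant blinding to the type of intervention is not feasible".
- **Section 2.5.2** defines the main Part 3 analysis as change in ODI from baseline to just after session 6, manipulation against health education. It gives an item-level rule for incomplete questionnaires. It does not say which patients enter the comparison.
- **Section 2.8** requires 18 patients per arm, then adds: "Considering a 20% attrition rate, 23 patients with LMS will be enrolled in the case intervention group", with the same number in the control arm.
- **Section 2.10** assigns ODI to repeated-measures ANOVA, or to generalized estimating equations in Part 3 if the data are not normal. Linear mixed models are named only for the fNIRS connectivity, wavelet and graph measures.
- **Section 2.9** says that missing-data rules have been clarified, but beyond the ODI item rule the article shows none.

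**The concern.** Entries (b) and (c), and most of (d), happen after allocation. The arms differ in ways that can drive them. Reactions to manual pressure can occur only where pressure is applied, and patients who know they were given education may disengage for their own reasons. If such patients leave the primary analysis, the two groups compared are no longer the two groups that were randomised, and a difference in ODI may partly reflect who was kept.

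This is more than silence about an analysis population, which an article may leave to a fuller document. The article states a rule, and the rule merges three actions with different consequences for the data. It also affects data collection. If ODI is not taken after a patient stops, no later analysis plan can recover it.

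**Working it through.** **1. What the list most naturally means.** The heading names elimination separately from termination and attrition. Entry (d) is attrition, and (c) fits termination. Entry (b), poor compliance, fits neither well, so removal from the data set is its natural home. Two other sections fit that reading: the sample size counts on 18 of 23 per arm, and the default ODI method normally drops any patient with an incomplete series. The GEE fallback uses the visits that are available, but it would not bring back a patient who had been eliminated. No section expressly says that eliminated patients leave the ODI comparison, and none says that all randomised patients stay in.

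**2. The plan's own figures.** Inputs from section 2.8: difference 10, SD 9, α = 0.05, power 0.80, attrition 20%.

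- Attrition step: 18 / 0.8 = 22.5, rounded up to 23. This reproduces. It leaves room to lose 5 of 23 (21.7%) per arm.
- Base size: n = 2 × [σ(z₀.₉₇₅ + z₀.₈₀)/Δ]² = 12.7, so 13 per arm (14 with the t distribution). The stated 18 does not reproduce at 80% power. It is close to 90% power (17.0, so 18, by the normal formula; t-test power at 18 is 0.899), or to 14 already inflated for dropout (14 / 0.8 = 17.5). That is a separate matter and errs towards more patients. The present point does not depend on it.

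**3. How much selective removal could matter (illustration).** Assumptions: true difference 0, SD 9, 23 per arm, t test, k patients removed from the intervention arm only, 100,000 simulated trials.

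| k removed | The k worst: bias (ODI points) | Two-sided rejection rate | k at random from the worse half: bias | Two-sided rejection rate |
|---|---|---|---|---|
| 1 | 0.8 | 6.7% | 0.3 | 4.9% |
| 3 | 2.1 | 13.7% | 1.1 | 6.3% |
| 5 | 3.2 | 24.7% | 2.0 | 10.1% |

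The range is wide because everything depends on who is removed. Removal from the control arm instead would reverse the sign.

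**4. Whether the planned size can carry an as-randomised analysis.** Suppose k intervention patients stay in the analysis and gain nothing. The difference becomes 10 × (23 − k)/23, with SD held at 9 and 23 per arm (two-sided t test).

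| k with no benefit | Difference | Power |
|---|---|---|
| 0 | 10.0 | 0.958 |
| 1 | 9.6 | 0.94 |
| 3 | 8.7 | 0.89 |
| 5 | 7.8 | 0.82 |

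All of these meet the planned 80%.

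**The case against.** The strongest reply is that section 2.2.3 says nothing about analysis. Serious reactions can be read as grounds for termination and lost contact as attrition, and neither implies deleting ODI values already collected. Section 2.5.2 defines the comparison by allocated group and does not restrict it to compliers. The analysis population may be set in a full protocol or analysis plan that is not shown. Adverse events go on the case report form, and Table 2 schedules compliance, adverse event assessment and reasons for dropout, so harmed patients do not vanish from the record.

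Much of this stands, and it rules out several stronger readings that a reader might infer:

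- **That the plan definitely excludes these patients.** No sentence says so.
- **That the 20% allowance replaces eliminated patients or sets a removal quota.** It is an ordinary inflation for expected loss and is compatible with an as-randomised analysis.
- **That the bias favours manipulation.** If the education patients who are doing worst leave, it runs the other way.
- **That the effect would be overstated by 25%.** A reader might compute 0.8 × 10 + 0.2 × 0 = 8 against 10. This assumes that a fifth of one arm gains nothing, that all of them are removed, and that nothing informative happens in the other arm. The document supports none of this.

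The reply does not remove the defect. Poor compliance is stated as a criterion under a heading that includes elimination. A later plan that analysed everyone would have to be reconciled with that text, and it could not supply ODI values that were never collected.

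**Conclusion.** The concern holds as a badly fixed rule with a possible consequence. Section 2.2.3 does not distinguish stopping the intervention from leaving the analysis. Combined with an ODI method that is complete-case in its usual form and no named as-randomised population, it permits the primary comparison in a participant-unblinded trial to be made on patients selected after randomisation, for reasons that can differ by arm.

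Neither the size nor the direction of the bias can be read from the document. The range of about 0.3 to 3.2 ODI points assumes a true difference of zero and the removal of 1 to 5 poorly responding patients from one arm only. The finding that an as-randomised analysis is affordable rests on the stated difference and SD, on an unchanged SD when non-benefiting patients are kept, and on ODI being obtained for all 23 per arm.

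**What to change.** 1. In section 2.2.3, separate the three actions. State that these criteria may end the intervention or describe dropout, but do not remove a randomised patient from the primary analysis. Which events end treatment remains a clinical matter and is not affected.
2. State in section 2.5.2 or 2.10 that the primary ODI comparison includes every randomised Part 3 patient in the allocated arm.
3. Continue to collect ODI at the session-6 time point after non-compliance or discontinuation, where the patient agrees.
4. Amend section 2.10 so that the ODI analysis uses all available data. A linear mixed model for repeated measures is one option. It must be named for ODI explicitly, because the section now assigns mixed models only to fNIRS measures.
5. Keep the current list solely to define a per-protocol set for a sensitivity analysis.

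The cost is some rewording, one extra questionnaire for each patient who stops, and possibly a smaller effect estimate. The enrolled number need not change on the stated inputs. Step 3 has to be in place before Part 3 patients begin to stop sessions.

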### Recruitment, randomization and blinding

2.3

#### Recruitment

2.3.1

This study is conducted in the outpatient departments of Tuina and Rehabilitation of Yueyang Integrated Traditional Chinese and Western Medicine Hospital Affiliated to Shanghai University of Traditional Chinese Medicine. Recruitment announcements are released through the hospital’s official social media accounts to maximize the visibility and accessibility of potential participants. Subjects are recruited on a voluntary basis, and all participants have to voluntarily sign the informed consent form and provide relevant information and data.

#### Randomization and blinding

2.3.2

Randomization is standardized in this study in combination with the design characteristics of the three parts of the experiment: The first part is a case–control observational study. After screening through strict inclusion and exclusion criteria, the case group (patients with lumbar muscle strain) and the control group (healthy people without lumbocrural pain) are selected from the eligible population by simple random sampling (15 cases in each group) to ensure sample representativeness, with no inter-group random allocation involved. The second part is a cross-over design study, in which 24 patients with lumbar muscle strain are divided into 3 groups (8 cases in each group) by complete randomization, receiving three sequences of rolling manipulation intervention with low-medium-high, medium-high-low and high-low-medium pressure, respectively. The third part is an interventional trial involving 69 participants in total. 46 patients with lumbar muscle strain are stratified by age and disease duration and then divided into a case intervention group (rolling manipulation intervention, *n* = 23) and a case control group (health education intervention, *n* = 23) by the random number table method; additionally, 23 healthy controls are selected by simple random sampling.

This study adopts a partial blinding method to control bias, and supplements standardized training for operators to reduce operation bias: At the participant level, in the crossover design of the second part, participants are unaware of the pressure level and intervention sequence. In Part 3, participant blinding to the type of intervention is not feasible because the case intervention group receives manual rolling manipulation whereas the case control group receives health education. Participants are not informed of the study hypotheses or the expected superiority of either intervention. Outcome assessors and statistical analysts remain blinded to group allocation. Data collection is performed by full-time researchers who do not participate in the interventions, and statistical analysts receive coded anonymous data; neither is aware of the grouping information. All operators receive unified standardized training for 3 times (2 h each time), including the calibration of manipulation pressure, frequency and operation position, and only pass the assessment (the consistency of manipulation parameters ICC>0.8) can they perform the intervention independently. Blinding is maintained by separating the intervention and data collection settings and formulating confidentiality protocols. The blind is only broken in accordance with procedures and documented in detail upon approval by the ethics committee in special circumstances such as the occurrence of serious adverse reactions in participants.

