The fluctuation ranges of the low, medium, and high pressure levels were calculated separately using the 95% confidence intervals: Fluctuation range (%) = (upper limit of 95%CI − lower limit of 95%CI) / (2 × mean) × 100%. The fluctuation range value (in Newtons) was then calculated as the mean multiplied by the fluctuation range percentage. For each pressure level, the lower limit of the interval was calculated as the mean minus the fluctuation range value, and the upper limit of the interval was calculated as the mean plus the fluctuation range value. The high-pressure level was applied strictly within the participant’s pain tolerance, and the operator’s physical capacity was also considered to avoid injury. After the pressure levels were determined, the Novel Pliance-X 32 Expert glove-type pressure distribution measurement system was used to measure the mechanical parameters of the rolling manipulation as an operational reference and to monitor standardization. The system is calibrated once a day before the operation to ensure the accuracy of pressure measurement. After the tuina pressure range is set, subsequent patients are strictly screened according to the “tuina pressure value range”determined by the experiment, and only subjects whose lumbar erector spinae bearing threshold fell within this range are included, and those beyond the range (too high/too low) are directly excluded.

A preliminary study was conducted before the formal trial to determine the washout duration. Six participants with lumbar muscle strain received a single session of rolling manipulation using clinically common parameters (4 kg, 120 times/min, 10 min). The root mean square (RMS) values of surface electromyography (sEMG) from the bilateral erector spinae were recorded before the intervention, immediately after the intervention, and on Days 3, 5, and 7 after the intervention. The RMS values increased immediately after the intervention, declined by Day 3, fell below the pre-intervention level by Day 5, and remained stable on Day 7. No statistically significant differences were observed between the pre-intervention values and those on Days 5 and 7, indicating that muscle activity had reached a stable state within 7 days. Accordingly, the washout period was set to 7 days (Table 1).

**Table 1 tab1:** RMS values of the bilateral erector spinae during the washout observation (*n* = 6).

Side	Baseline	Immediately after intervention	Day 3	Day 5	Day 7

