### Quality control

2.7

Random grouping and control design are adopted, the basis for sample size calculation is clarified, a standardized research manual is formulated, and all researchers take up their posts only after passing pre-job training. A supervision group and inspectors are set up, subjects are strictly screened during recruitment, and baseline data between groups are calibrated. For the crossover design in Part 2, the 7-day washout period duration is specifically justified by preliminary observation data to minimize potential carryover effects between successive interventions. Intervention operations are performed by fixed personnel, and manipulations and instruments are regularly calibrated. Detection data follow unified operating specifications, a double entry and review system is adopted, and missing and abnormal data are handled in accordance with regulations. Appropriate methods are selected for statistical analysis with multiple comparison correction, which is completed by professionals with analysis codes retained. Paper and electronic data are managed in a standardized manner throughout the process to ensure research traceability and reliable results.

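### The three Part 2 sequences give each pressure only one possible predecessor, and the six-patient washout pilot is too small and narrow to make that safe; using all six orders would cost nothing

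*Protocol article*

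**What the plan says.** Section 2.3.2 of the protocol article fixes the orders for Part 2 as "three sequences of rolling manipulation intervention with low-medium-high, medium-high-low and high-low-medium pressure". Patients are allocated to these orders at random, eight to each. Section 2.4.2 repeats the same three orders. The reverse orders (low-high-medium, medium-low-high, high-medium-low) are not used.

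Section 2.5.2 defines the primary outcomes as the changes in sEMG RMS and MF from before to immediately after each session, compared between pressures within patients.

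Carryover is addressed through the washout. Section 2.7 states that "the 7-day washout period duration is specifically justified by preliminary observation data to minimize potential carryover effects between successive interventions". Section 2.4.2 describes those data: six patients, one session at 4 kg, and RMS of the erector spinae followed to Day 7. The inference drawn is "No statistically significant differences were observed between the pre-intervention values and those on Days 5 and 7", from which the text concludes that muscle activity was stable within 7 days.

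Section 2.10 plans repeated-measures ANOVA, or the Friedman test for non-normal data, across the three pressures.

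**The concern.** A crossover that balances period protects against time trends. Protection against carryover needs either balance over predecessors or good evidence that there is no carryover. This design lacks the first, and the evidence offered for the second is thin. If one pressure alters how the muscle responds at the next session, that alteration always falls on the same neighbouring pressure and looks like an effect of that neighbour.

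Part 2 selects the pressure used in Part 3, so an order artefact could influence which level goes forward.

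**Working it through.** **Inputs.** 24 patients, 8 per sequence, three periods (section 2.3.2); 17 evaluable and 20% attrition (section 2.8); pilot means and SDs (Table 1, n = 6). Two things are assumed: a first-order carryover model, and the correlation r between a patient's baseline and Day 7 values, which is not reported and is varied.

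**The plan's own number.** Section 2.8 says "PASS 2021 software calculation showed that 17 cases are needed". 17 / 0.80 = 21.25, so 22, and the next multiple of three is 24, as stated. The 17 cannot be re-derived because no effect size is given. 24 is also a multiple of six.

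**Predecessors, 8 patients per sequence.**

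| Pressure | First | After low | After medium | After high |
|---|---|---|---|---|
| Low | 8 | – | 0 | 16 |
| Medium | 8 | 16 | – | 0 |
| High | 8 | 0 | 16 | – |

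**Bias without a carryover term.** Let c_L, c_M and c_H be the carryover left by each level. Each pressure is given 24 times, 16 of them after its one predecessor, so its mean shifts by 16/24 = 2/3 of that predecessor's carryover. For example, low minus medium shifts by (2/3)(c_H − c_L). Adjusting for period leaves this unchanged. Equal carryover from all levels cancels. With all six orders, each pressure follows each other pressure 8 times, the multiplier is 8/24 = 1/3, and low minus medium shifts by (1/3)(c_M − c_L).

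**Variance.** Var = σ² k′(X′X)⁻¹k for a pairwise pressure contrast k, where X holds participant, period and pressure (28 parameters, 72 observations), or these plus first-order carryover (30 parameters, rank 30).

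| Design | No carryover term | With carryover term | Ratio |
|---|---|---|---|
| Three orders, 8 each | 0.0833 σ² (= 2/24) | 0.4167 σ² | 5.0 |
| Six orders, 4 each | 0.0833 σ² | 0.1042 σ² | 1.25 |

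Adjusting in the current design loses 1 − 1/5 = 80% of the information; with six orders it loses 1 − 1/1.25 = 20%. The adjusted standard error falls from √0.4167 = 0.645 σ to √0.1042 = 0.323 σ, a half.

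**Washout pilot (Table 1).**
- Left: immediate change 54.37 − 48.39 = +5.98 µV; Day 7 change 41.16 − 48.39 = −7.23 µV.
- Right: immediate change 49.92 − 45.46 = +4.46 µV; Day 7 change 43.10 − 45.46 = −2.36 µV.

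The 95% interval for the Day 7 change is difference ± 2.571 × SD_d/√6, with SD_d² = s₀² + s₇² − 2r·s₀·s₇.
- Left, r = 0.5: SD_d = √(19.42² + 4.58² − 19.42 × 4.58) = 17.6, giving −25.7 to +11.2 µV.
- Left, r from 0 to 0.9: from (−28.2, +13.7) to (−23.4, +9.0).
- Left, limiting case r = 1: SD_d = 19.42 − 4.58 = 14.84, half-width 15.6, giving −22.8 to +8.3. No correlation gives a narrower interval.
- Right, r from 0 to 0.9: from (−24.6, +19.9) to (−9.5, +4.8).

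Each of these intervals contains zero and also contains changes as large as the immediate effect in either direction. Power to detect a Day 7 change of that size is about 9–12% on the left and 7–26% on the right for r from 0 to 0.9.

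**The case against.** The strongest defence is that the design already handles the obvious form of carryover. The outcome is a change from a measurement taken before each session, so a shift in resting level that persists for a week is subtracted out. This stands. Table 2 lists only one pre-intervention column for Part 2, but the text of sections 2.5.2 and 2.5.3 calls for measurement before each session, and I take the text as governing. Only altered responsiveness remains, and no figure in the documents bears on it.

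A reader might infer that pressure and carryover cannot be separated at all. That is too strong: each pressure comes first in one sequence, so the carryover model has full rank. The problem is efficiency, not identifiability.

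A reader might also infer from Table 1 that RMS failed to return to baseline, because 7.23 exceeds 5.98. The table does not support this. The Day 7 difference has the opposite sign to the immediate effect, its interval includes zero, and the means are level from Day 5 to Day 7 (42.16 to 41.16 left; 42.33 to 43.10 right). With SDs of 19.42 and 4.58, a few high baseline values could produce the gap.

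Three further points stand. Period and carryover terms are commonly left to an analysis plan, so their absence from section 2.10 is not a fault. The protocol speaks of minimising carryover and does not claim to have eliminated it. And Part 3 randomises the selected pressure against health education, so a poor selection would not bias that comparison.

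None of this repairs the allocation. An analysis plan can add a carryover term, but with these three orders it pays the fivefold variance, and the Friedman option cannot carry such a term.

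**Conclusion.** The point holds as a weakness of design for which a better alternative is available at no cost; it does not show that Part 2 is biased. The predecessor imbalance follows directly from the stated sequences. The 2/3 multiplier and the variance ratios (5 against 1.25) assume an additive first-order carryover model with 24 completers. The carryover itself is of unknown size and, given the change score, would have to act through altered responsiveness.

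The pilot is inconclusive in both directions. It covers six patients, one pressure and RMS only. MF (the outcome used to size Part 2), isokinetic strength, muscle tension and pressure pain threshold are not reported in it, and the three study pressures were not compared. Non-significance there cannot bear the weight that an order-unbalanced design puts on it. That the left-side comparison is inconclusive does not depend on the assumed correlation.

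I would grade this as a recommended improvement, not an essential correction.

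**What to change.** 1. Before Part 2 is randomised, allocate the same 24 patients to all six orders, adding low-high-medium, medium-low-high and high-medium-low, four per sequence. This needs a new randomisation list and no extra patients or visits. Precision is unchanged if carryover is absent (0.0833 σ² either way), and the carryover-adjusted standard error is halved. The multiplier on unadjusted bias falls from 2/3 to 1/3; bias is halved, not removed.
2. Fit participant, period and pressure, with first-order carryover as a pre-planned sensitivity term.
3. The article mixes tenses about allocation, so it is unclear whether Part 2 has already been randomised. If it has, keep the sensitivity analysis and report its fivefold variance cost alongside it.
4. Reword sections 2.4.2 and 2.7 to say that the pilot is limited to RMS at one pressure in six patients and does not exclude carryover.
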